### Analysis

#### Primary and secondary RCT outcomes

The primary analysis will be performed according to intention to treat, including all clusters and participants in the allocated groups. Between-group difference for both primary outcomes (health provider and older people) will be analysed using mixed effects regression models with a fixed effect for the intervention group and random effect for participants to account for repeated measures. Cluster site will also be added as a random effect. Due to the likelihood of differences across sites, a number of baseline covariates will be controlled for in the analyses (as listed in Table 2).

**Table 2 Tab2:** List of covariates to be used in analysis and source

	*Health provider outcomes*	*Older adult outcomes*
*Self-reported*	Profession, age, gender, years in the role	Age, sex, ethnicity, location, educational and economic attainments, country of birth, English proficiency, reason for subacute stay, and admission to any other hospital in the trial
*Reported by site champion based on data routinely collected by hospitals, or case records*	General characteristics of the site (size of workplace, location, subacute services offered), average characteristics of older patient cohorts admitted to the participating wards (age, gender, country of birth, English proficiency, reason for subacute stay), and elder abuse cases (number of suspected elder abuse cases p/month, number, and types of referral) to enable the evaluation and statistical control of differences between sites	Length of hospital admission, length of admission on participating ward; number of eligible clinicians (total and by profession), and number of clinicians who have completed the training (total and by profession) to provide a measure of ‘dose’

We will similarly analyse secondary outcomes. Continuous outcomes will be analysed using mixed effects linear regression models and adjustment for baseline values. Statistics will be reported with their respective 95% confidence intervals and *P* values. Per-protocol analyses will also be performed, omitting participants with predefined protocol deviations (e.g. allocated intervention not received, violated inclusion/exclusion criteria). The trial results will be reported in line with the CONSORT extension for cluster trials. As this is a low-risk, non-medical intervention, no interim analyses will be conducted, and no stopping guidelines were developed for ceasing the trial early. Similarly, as adverse events reporting is only required for medical interventions, we do not report these.

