#### Older people

Older people will complete a demographic survey (age, gender, education, postcode, country of birth, language/s spoken, English language skills, First Nations status, reason for admission and underlying health risk factors for elder abuse (e.g. dementia, mobility), the Adult Social Care Outcomes Toolkit (ASCOT) [31] (primary outcome), the Short Form Survey-12 (SF-12v2) [32], and an adapted Resource Utilisation in Dementia lite (a-RUD-lite) (secondary outcomes) via online/paper/telephone survey. Site champions will support older people where required and record the older person’s length of admission once discharged.

**Table 1 Tab1:** Procedure timeline

**Procedures**	**Assessment/procedure**	**Screening**	**Baseline**	**4-month follow-up**	**9-month follow-up**

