	**Older adults**				
	** Informed consent**	**x**			
	** Demographic Information**		**x**		
	** ASCOT questionnaire**		**x**	**x**	**x**
	** SF-12v2 questionnaire**		**x**	**x**	**x**
	** a-RUD-lite questionnaire**		**x**	**x**	**x**
	** Has patient attended another hospital in trial during study period**		**x**	**x**	**x**
	**Administrative/site data**	**9 months prior to Baseline**	**Baseline**	**Baseline to 4 months**	**4-months to 9 months**
	** Elder abuse cases**	**x**	**x**	**x**	**x**
	** Elder abuse referrals**	**x**	**x**	**x**	**x**
	** Nature of referral**	**x**	**x**	**x**	**x**
	** Number of eligible clinicians (total and by profession)**		**x**	**x**	
	** Number of clinicians who have completed the training (total and by profession)**		**x**	**x**	
	** Number of times the screening tool was administered/not administered**		**x**	**x**	**x**

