### Limitations

We will exclude patients who receive subacute care at home, despite this being an increasingly popular model of care. This minimises the risk of screening in the presence of a perpetrator, which would reduce the likelihood of disclosing abuse and may pose risks to the older person and/or care staff.

Second, we will exclude older adults without the capacity to consent to research participation to avoid seeking proxy consent from a substitute decision maker, which could include a perpetrator of abuse.

Finally, the recruitment of older people by site champions after randomisation introduces a risk of bias as site champions will know whether they are in the intervention or control arm. This common problem with cluster RCTs will be managed in the analytic strategy (e.g. through difference-in-differences techniques).

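### Table 2 leaves the health risk factors already collected (such as dementia and mobility) out of the older-adult covariates, although patients are recruited after randomisation by champions who know the allocation

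*Protocol article*

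**What the plan says.** The Analysis section of the protocol article (Primary and secondary RCT outcomes) says that "a number of baseline covariates will be controlled for in the analyses (as listed in Table 2", giving likely differences across sites as the reason. For older-adult outcomes the self-reported cell of Table 2 reads "Age, sex, ethnicity, location, educational and economic attainments, country of birth, English proficiency, reason for subacute stay"; its one further item is a stay at another participating hospital. The cell completed by site champions adds length of admission, numbers of eligible clinicians and numbers who finished the training. Neither cell names a health condition.

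Under Outcome assessments, Older people, the survey is listed as "age, gender, education, postcode, country of birth, language/s spoken, English language skills, First Nations status, reason for admission and underlying health risk factors", and the last item is spelled out as "underlying health risk factors for elder abuse (e.g. dementia, mobility". Table 1 adds the item "Has patient attended another hospital in trial during study period".

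Three further statements bear on the point. The Limitations section accepts that "the recruitment of older people by site champions after randomisation introduces a risk of bias", because champions know their arm, and says the analysis will manage this, with difference-in-differences as an example. The Recruitment section says older people are enrolled only after intervention-arm staff have done the training and the screening tool is in use. The Analysis section plans adjustment for baseline values of continuous outcomes.

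**The concern.** In a cluster trial whose patients are identified before allocation or independently of it, leaving a prognostic variable out of the model costs some precision and does not by itself bias the comparison. This trial lacks that protection at patient level. Champions who know the allocation approach and enrol the patients, so the kind of patient enrolled can differ by arm. With five sites per arm, chance imbalance is also plausible.

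The natural remedy is to adjust for patient characteristics that the intervention cannot have changed. Dementia and mobility limitation largely predate admission and are unlikely to be altered by staff training, and the survey already records them. Leaving them out means the co-primary ASCOT comparison depends on age, reason for stay and the first ASCOT score to absorb differences in health. That first score is taken when the intervention may already be acting.

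A smaller matter is that Table 2 asks for a self-reported economic covariate that the survey, as described, does not contain.

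**Working it through.** The document states no figure for this point, so there is none to reproduce. The check has three parts.

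**1. Matching the lists.** Table 2 has 10 self-reported older-adult covariates, set here against the survey list and Table 1.
- Seven have a match: age, location (postcode), education, country of birth, English proficiency, reason for stay, and admission to another trial hospital (Table 1).
- One differs in label: sex in Table 2, gender in the survey.
- One is covered only indirectly: ethnicity, through First Nations status, country of birth and language.
- One has no described source: economic attainment.
- In the other direction, the health risk factors are in the survey but in neither older-adult cell of Table 2.

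**2. What the planned safeguards remove.** Let Δ be the between-arm difference in prevalence of a condition. Let β0 and β1 be its effect on ASCOT at the first and 4-month assessments, τ0 and τ1 the intervention effect at those times, and ρ the coefficient on the first ASCOT. The between-arm contrast then estimates:
- No adjustment: τ1 + β1Δ.
- Difference-in-differences: (τ1 − τ0) + (β1 − β0)Δ.
- Adjustment for the first ASCOT: (τ1 − ρτ0) + (β1 − ρβ0)Δ. If β0 = β1 = β, the case-mix term is (1 − ρ)βΔ.

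Differencing therefore removes a stable effect of the condition, but not an effect on change over time. It also subtracts any intervention effect already present at the first assessment. Baseline adjustment leaves a fraction 1 − ρ of a stable effect. Adding the condition to the model removes its Δ term, as far as the condition is recorded accurately. It does not touch τ0.

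**3. Size, on assumptions.** The document gives no values for Δ, β or ρ. Assume that a condition lowers ASCOT by 0.25 to 0.75 SD and that its prevalence differs between arms by 5 to 20 percentage points.
- Bias before any adjustment = Δ × β: from 0.05 × 0.25 = 0.0125 SD to 0.20 × 0.75 = 0.15 SD.
- With the SD of 0.2 in the Sample size section: 0.0125 × 0.2 = 0.0025 to 0.15 × 0.2 = 0.03 ASCOT units.
- The Sample size section plans for a medium ASCOT effect without giving a value. If that means 0.5 SD, the ratio is 0.0125/0.5 = 2.5% to 0.15/0.5 = 30%.

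These are values before adjustment. Since ρ and the change from β0 to β1 are unknown, the residual after the planned analysis cannot be computed.

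For precision, take ICC 0.1 and 40 patients per site (Sample size section), and assume the added terms explain 10% of within-site variance. The variance of a site mean, in units of the total variance, falls from 0.1 + 0.9/40 = 0.1225 to 0.1 + 0.81/40 = 0.12025. The reduction is 0.00225/0.1225 = 1.8%.

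**The case against.** The case against acting is substantial.
- The choice of adjustment set is a design decision, and nothing in the document says every recorded item must become a covariate.
- The survey calls these conditions risk factors for elder abuse, not predictors of ASCOT.
- People without decision-making capacity are excluded, which narrows the range of dementia in the sample.
- Baseline adjustment and difference-in-differences are planned, and age and reason for stay already carry some case-mix.
- Dementia and mobility are only examples, and how they are recorded is not stated.
- The article is condensed, so its survey list may be shortened and an economic item may exist.

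Much of this stands. It rules out calling the omission an error and makes the economic mismatch a matter of wording. It does not remove the reason to add the terms. The exclusion leaves milder dementia and all variation in mobility. The planned safeguards rest on a first ASCOT measured after the intervention has begun, and they remove a stable case-mix effect fully only under differencing.

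A reader might go further and infer that the ASCOT model cannot be fitted, or that key confounders have been left out. The document supports neither. One of 10 self-reported terms lacks a described source and the others can be used. No evidence is given that dementia or mobility differs between arms or drives ASCOT here.

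The same Table 2 column also contains quantities that arise after randomisation, namely training completion and length of admission. That is a separate matter, which this change does not settle.

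**Conclusion.** The point holds as a well-grounded improvement to the covariate list. Patient-level health risk factors that the trial already collects are missing from the older-adult adjustment set. The trial's own account of recruitment after randomisation by unblinded champions, together with a first ASCOT taken once the intervention is running, means that case-mix imbalance may not be fully removed.

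The size of the residual bias is unknown. The range of 0.0125 to 0.15 SD rests on assumed prevalence differences and effects, and applies before any adjustment. Reading its upper end as a 30% distortion of the co-primary result would be wrong, because the planned model adjusts for baseline and the 0.5 SD denominator is itself an assumption. The precision gain is small. The argument assumes that dementia and mobility limitation are not changed by the intervention and are recorded comparably in both arms.

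The economic-attainments mismatch is real but minor, and does not stop the rest of the model being fitted.

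**What to change.** In Table 2, older-adult column, add the underlying health risk factors from the survey as patient-level baseline covariates in the ASCOT model. State which conditions are included and how each is coded, before outcome data are analysed by arm. The cost is a few more model terms and a change of wording, with no new data collection. The addition does not correct for the late first ASCOT, so the baseline and difference-in-differences results still need to be interpreted with that timing in mind.

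Separately, reconcile economic attainments between Table 2 and the survey description in one of three ways:
- confirm that the item is collected and add it to the survey list;
- replace it with an area-level index derived from postcode, relabelled as not self-reported;
- delete it from Table 2.

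As the article reports that recruitment has begun, this is best settled now: if the item is not being collected, it becomes harder to recover with time.

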**Methods:**

This is a single-blinded, pragmatic, cluster randomised controlled trial. Ten subacute hospital sites (i.e. clusters) across Australia will be allocated 1:1, stratified by state to a multi-component intervention comprising a training programme for health providers, implementation of a screening tool and use of site champions, or no additional training or support. Outcomes will be collected at baseline, 4 and 9 months. Our co-primary outcomes are change in health providers’ knowledge of responding to elder abuse and older people’s sense of safety and quality of life. We will include all inpatients at participating sites, aged 65 + (or aged 50 + if Aboriginal or Torres Strait Islander), who are able to provide informed consent and all unit staff who provide direct care to older people; a sample size of at least 92 health providers and 612 older people will provide sufficient power for primary analyses.

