### Group allocation

Stratified randomisation will allocate clusters (subacute sites) to either intervention or wait list control using a minimisation procedure. State (VIC, NSW, SA, WA) is a stratification factor. This is a single-blinded study where the statistician and outcome assessors will be blinded to allocation. Randomisation will occur following completion of baseline data collection for health providers. An independent biostatistician who is not a member of the research team will generate the allocation sequence. It is not possible to blind participants to group allocation when collecting the post-intervention scores. During the assessment period, we will ask health provider participants not to discuss the study outside their site.

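### The provider model commits to at least 9 to 11 site-level covariates with only 10 sites, so the KAMA arm main effect is not identified as specified

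*Protocol article*

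**What the plan says.** The Abstract (Methods) sets the number of randomised units: "Ten subacute hospital sites (i.e. clusters) across Australia will be allocated 1:1, stratified by state". The Sample size section confirms 5 intervention and 5 control clusters.

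Under Analysis, Primary and secondary RCT outcomes, both primary outcomes are to be analysed with "mixed effects regression models with a fixed effect for the intervention group and random effect for participants to account for repeated measures", and "Cluster site will also be added as a random effect". The same paragraph adds that "a number of baseline covariates will be controlled for in the analyses (as listed in Table 2").

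In Table 2, the provider column has four self-reported individual items (profession, age, gender, years in role). It then has a block supplied by the site champion, which opens with "General characteristics of the site (size of workplace, location, subacute services offered), average characteristics of older patient cohorts admitted to the participating wards". Five such ward averages are named, covering patients' age, gender, birthplace, command of English and why they were admitted. The block ends with monthly counts of suspected abuse, and how many referrals were made and of what type.

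Table 2 gives statistical control of site differences as a purpose of this block, so it is not offered for description alone. No rule for choosing among the variables is stated. The paragraph after Table 2 says continuous outcomes are adjusted for their baseline values.

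**The concern.** Arm is assigned by site, so every provider at a site has the same arm value, and the arm effect is estimated from differences among 10 site-level quantities. Each site-level covariate uses up one of those differences. The site block in the provider column contains more variables than 10 sites can support alongside an intercept and an arm term.

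At stake is one of the two co-primary analyses. If arm can be written exactly as a combination of the covariates, the model returns no unique intervention effect. Software would usually drop columns by its own rule, often by order of entry. Otherwise the list would have to be shortened at analysis, by a rule this document does not give. Either way, the covariate set in the primary KAMA analysis would not be the one the protocol states.

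**Working it through.** **Inputs.** Sites: 10, 5 per arm (Abstract; Sample size). Model: fixed arm effect, random participant and site effects, Table 2 covariates (Analysis). The plan gives no covariate count or degrees of freedom, so there is no figure of its own to reproduce.

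**Step 1, count the site-level variables in the provider column.**
- Site characteristics: 3 (size, location, services).
- Ward averages: 5 (age, gender, country of birth, English proficiency, reason for stay).
- Abuse and referral data: 3 (suspected cases per month, number of referrals, types of referral).
- Total: 3 + 5 + 3 = 11. Most lenient count, with all abuse and referral data as one variable: 3 + 5 + 1 = 9.

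Both counts give each variable one df. Services offered, reason for stay or referral type would each cost more if coded as categories.

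**Step 2, compare with what 10 sites allow.** Columns that are constant within site can have rank at most 10. Intercept and arm use 2, leaving 10 − 2 = 8. With 11 covariates there are 2 + 11 = 13 site-level columns and rank 10; with 9 there are 11 columns and rank 10. Once the intercept and 9 linearly independent site covariates are in, they span all 10 dimensions and arm is an exact combination of them.

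Individual-level covariates do not undo this dependence. Nor does the random site effect, because the redundancy lies in the fixed-effect columns whatever the covariance structure.

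**Step 3, rank check.** Design matrices for 10 sites (5 v 5) were built with k simulated continuous site covariates. Variance inflation is the median over 4,000 draws of independent normal covariates. It illustrates the pattern and does not predict the values for these sites.

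| k | Site-level columns | Rank | Between-site df left | Arm main effect estimable | Median variance inflation of arm effect |
|---|---|---|---|---|---|
| 0 | 2 | 2 | 8 | yes | 1.0 |
| 2 | 4 | 4 | 6 | yes | 1.2 |
| 4 | 6 | 6 | 4 | yes | 1.8 |
| 6 | 8 | 8 | 2 | yes | 3.2 |
| 7 | 9 | 9 | 1 | yes | 5.7 |
| 8 | 10 | 10 | 0 | yes | 15.9 |
| 9 | 11 | 10 | 0 | no | – |
| 11 | 13 | 10 | 0 | no | – |

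Dropping every abuse and referral item still leaves 3 + 5 = 8. Arm is then formally estimable, but no between-site information remains with which to judge its precision.

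**Step 4, the alternative contrast.** With baseline KAMA kept as an outcome and arm-by-time as the target, the same check finds the 4-month contrast estimable even with 11 site covariates, because that column varies within site.

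**The case against.** The strongest defence is that the intended estimand may be an arm-by-time contrast. The Abstract describes the co-primary outcomes as change, the model has a participant effect for repeated measures, and Limitations mentions difference-in-differences. Such a contrast would survive the full covariate list, so it would be wrong to infer that no intervention effect could be obtained from these data under any model. However, the analysis section names only a fixed effect for group, with adjustment for baseline. The difference-in-differences remark concerns recruitment bias among older people. A change score analysed with an arm main effect would have the same identification problem.

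A second defence is that an unseen analysis plan may narrow the list. It may, but this document goes beyond leaving the matter open: it says the listed covariates will be controlled for.

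Three further inferences are tempting and not supported:
- **Inflated type I error from Wald tests on 10 clusters.** The protocol promises confidence intervals and P values but names no test, reference distribution or df method. That choice is commonly left to the analysis plan.
- **Omission of the stratification factor.** Group allocation says "State (VIC, NSW, SA, WA) is a stratification factor", and Table 2 lists location, which may encode state.
- **The same failure in the older-adult model.** The 11 variables are in the provider column only. The older-adult column's clinician counts, for the three staff groups named under Participants and setting, come to about 6 df (3 eligible, 3 trained, totals being sums). That is within the limit of 8.

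**Conclusion.** The point holds for the provider model as written. With 11 site-level covariates, or 9 on the most lenient count, and 10 sites, the main effect of arm on KAMA is not identified; the limit is 8, and 8 leaves no between-site df. This rests on three assumptions: each listed variable enters with at least one df, the site variables are not exactly collinear with one another, and the target is an arm main effect with baseline as a covariate, which is the literal text. The conclusion does not depend on any ICC, effect size or sample size.

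**What to change.** In the analysis section and the provider column of Table 2, restrict the primary KAMA model to arm, baseline KAMA, the individual-level covariates (profession, age, gender, years in role) and at most one of the following:
- state, the stratification factor, at 4 − 1 = 3 df; or
- one or two named, pre-specified site variables.

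Move the other site characteristics, ward averages and abuse and referral data to descriptive tables or to sensitivity models that add one at a time. If an arm-by-time contrast is what is meant, write that term into the model explicitly. The short list is still advisable in that case.

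**Cost.** This is a change of wording and needs no new data. The primary model will adjust less for differences between sites. With state in the model, 10 − 2 − 3 = 5 between-site df remain instead of 8. The critical t is then 2.57 instead of 2.31 at the 5% level, a multiplier about 11% larger (2.57/2.31 = 1.11). At the 1% level used to size the provider outcome it is about 4.03 instead of 3.36, about 20% larger (4.03/3.36 = 1.20). One or two site variables in place of state would leave 7 or 6 df.

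As advice only, the analysis plan should name a small-sample df method suited to 10 clusters, such as Kenward-Roger or Satterthwaite.

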### Intervention

This intervention comprises 3 components:(i)*Training*: Health provider participants will be asked to complete training via an online Learning Management System (Acorn) hosted by the National Ageing Research Institute (NARI). The training takes ~ 60 min to complete and is self-paced, and participants will have access to it over a 2-month period. It has four modules on knowledge of abuse, drivers of abuse, screening for abuse (including how to administer the Australian Elder Abuse Screening Instrument [AUSI]) [24], and management of elder abuse (further details available through the online trial registry anzctr.org.au, registration #ACTRN12623000676617p). This training was co-designed through workshops, interviews, and user-testing with health providers, family carers, older people, and elder abuse survivors. Site champions will promote completion of the training, with the aim of at least 60% of eligible health providers on participating wards completing the training over a 2-month period.(ii)*Screening tool*: Intervention sites will be provided with the AUSI screening tool, which has content validity [24], and has been demonstrated to increase staff confidence in screening for abuse and the proportion of cases of suspected abuse that provoked multidisciplinary responses [25]. Following the training, health providers will be asked to screen all patients for elder abuse and to manage detected cases as per usual practice, including referrals to outside agencies, but with support from the site champion where required.(iii)*Site champion*: Each site will recruit an on-site clinician (senior social worker or other staff with commensurate experience) as a site champion, who will support other hospital staff in screening and managing elder abuse. They will be trained by the research team and work 1 day per week supporting the intervention. Site champions will encourage uptake of the training and the AUSI and regularly contact staff to assess concerns and/or challenges encountered with screening. Site champions will be contacted every 2–3 weeks via email/phone by the research team to proactively support them and build a national peer-support network [26].

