### Control

The control arm will be waitlisted and given access to the training after 9 months. Control arm sites will also recruit site champions, who will be trained and supported in data collection. They will encourage completion of the outcome measures for health providers, recruit older people and collect data, and collect deidentified site data but will not provide further input beyond their normal clinical role.

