#### Sites

Site champions will obtain summary statistics routinely collected by hospitals such as general site characteristics (size of workplace, location, subacute services offered) and characteristics of patients admitted to participating wards (age, gender, country of birth, English proficiency, reason for subacute stay). They will also ascertain the number of eligible health providers to enable the calculation of the percentage who complete the training. Elder abuse detection and referral data will be collected from the 9 months preceding the trial to the end of the trial (i.e. at completion of 9-month outcomes). Specifically, site champions will screen medical records of all inpatients on participating wards during that time to ascertain (i) number of records screened, (ii) number of cases that identified elder abuse and the types, (iii) referrals made to social work, and (iv) the frequency of interventions and referrals (e.g. legal referral, safety planning) using a standardised template that will be provided. In the intervention arm, the number of times the AUSI screening tool is administered and not administered will also be collected; however, the responses on the AUSI will not be collected.

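### For the older-adult outcomes, Table 2 lists post-randomisation variables as baseline covariates, above all training dose, which nearly duplicates arm across ten sites

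*Protocol article*

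**What the plan says.** The Analysis section (Primary and secondary RCT outcomes) promises an intention-to-treat analysis using mixed models with a fixed effect for arm and random effects for participant and site. It then says that "a number of baseline covariates will be controlled for in the analyses (as listed in Table 2"). Table 2 is titled "List of covariates to be used in analysis and source".

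The older-adult column of Table 2 includes:
- "number of clinicians who have completed the training (total and by profession) to provide a measure of" dose, together with the number of eligible clinicians;
- "Length of hospital admission, length of admission on participating ward";
- admission to any other hospital in the trial.

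On timing, the protocol says:
- Group allocation: "Randomisation will occur following completion of baseline data collection for health providers".
- Intervention: sites have "the aim of at least 60% of eligible health providers on participating wards completing the training over a 2-month period".
- Control: "The control arm will be waitlisted and given access to the training after 9 months".
- Recruitment: older people enter only once intervention-arm training is complete and the screening tool is in use.
- Outcome assessments (Older people): length of admission is recorded after discharge.
- Table 1: attendance at another trial hospital is asked at baseline, 4 months and 9 months.

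**The concern.** A covariate is safe in a randomised comparison if allocation cannot change it. The number of clinicians trained is produced by allocation. A model containing both arm and dose does not estimate the effect of being allocated to the intervention. Its arm coefficient is the fitted difference between a control site and an intervention site in which nobody was trained, a site that the trial is designed not to have.

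Two things are at stake for the ASCOT. Precision suffers because arm and dose compete for the same contrast among ten sites. Bias arises to the extent that the intervention works through trained staff, because that part of the effect is credited to dose. Length of stay, and other-hospital admission recorded at follow-up, can also distort the contrast if the intervention affects them.

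**Working it through.** **Inputs from the Sample size section.** Five sites per arm, 40 older people per site, ICC 0.1, SD 0.2, 5% significance (two-sided assumed). A medium effect is taken as d = 0.5, as defined there for the KAMA, which gives 0.5 × 0.2 = 0.10 on the ASCOT.

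**Assumptions not in the protocol.** The between-site spread of percentage trained, the number of eligible staff per site, and the share of the effect that is proportional to dose. Control dose of zero is inferred from the waitlist rule.

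**1. Starting point without dose.** Arm and dose are both site-level, so site means suffice.
- Variance of a site mean: 0.2² × (0.1 + 0.9/40) = 0.04 × 0.1225 = 0.0049.
- SE of the arm effect: √(0.0049 × 2/5) = 0.0443.
- Power for 0.10: 62% by normal approximation, 51% by t on 8 df.

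The stated 80% is not reproduced. That is a separate matter, and nothing below depends on it.

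**2. Variance with dose added.** With dose zero in all controls, the dose slope is estimated from the five intervention sites alone. The variance of the arm coefficient is therefore multiplied by

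1 + d̄² / (0.4 × S), where d̄ is mean dose in intervention sites and S = Σ(dᵢ − d̄)².

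Five equally spaced sites with mean 0.6 (d̄² = 0.36):

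| Doses | S | Variance ratio | Arm–dose correlation | SE of arm | Power if the full 0.10 stays with arm (t, 7 df) |
|---|---|---|---|---|---|
| 50–70% | 0.025 | 1 + 0.36/0.01 = 37 | 0.99 | 0.269 | 6% |
| 40–80% | 0.10 | 1 + 0.36/0.04 = 10 | 0.95 | 0.140 | 10% |
| 20–100% | 0.40 | 1 + 0.36/0.16 = 3.25 | 0.83 | 0.080 | 19% |

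Tighter spreads inflate the variance further. If all intervention sites had the same percentage, arm and dose would be perfectly collinear and the arm effect could not be estimated.

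**3. Bias, with dose as a percentage.** Simulation of 6,000 trials per scenario, mean dose 60%, between-site SD 5, 10 or 20 points, true effect 0.10. Without dose, the estimate is about 0.10 with power 46–51%. With dose:

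| Share of effect proportional to dose | Median arm coefficient | Power |
|---|---|---|
| All | 0.001 to 0.009 | about 5% |
| Half | 0.044 to 0.053 | 5–7% |
| None | 0.101 to 0.106 | 6–12% |

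**4. Bias, with dose as a count, as Table 2 lists it.** Assumed 30–90 eligible staff per site, 45–80% trained, effect 0.5 SD and wholly proportional to percentage trained. The arm estimate averages about 0.4 SD with the trained count alone and about 0.3 SD with trained and eligible counts together. Median variance inflation is about 7 and 12, and power about 7–9%. Under the same set-up with percentage as the covariate, the estimate averages about 0 with inflation of about 26.

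**5. Other items.** The protocol gives no figure linking the intervention to length of stay or to admission elsewhere, so no bias can be computed for them.

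**The case against.** **Dose may be meant only for a secondary analysis.** The Recruitment section presents dose as something to capture for each site, and an exploratory use would be sensible. But nothing confines it to one, while the title of Table 2 and the sentence pointing to it place it in the models. Table 1 does schedule a training count at baseline. A count taken before training would be zero everywhere and could not measure dose.

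**A reader might infer that adjustment simply removes the intervention effect.** That holds only if the whole effect is proportional to percentage trained. The intervention also has a screening tool and a site champion, and with the counts that Table 2 lists much of the coefficient survives. This objection stands: the loss of precision is the robust harm, and the bias is conditional.

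**A reader might extend the point to the KAMA model.** The protocol does not support that. Training counts, length of stay and other-hospital admission appear only in the older-adult column. The provider column does list abuse cases and referrals, and the Sites section says "Elder abuse detection and referral data will be collected from the 9 months preceding the trial to the end of the trial". That is a data-collection window, not a covariate window. Table 1 has a separate column for the 9 months before baseline, and the covariates are called baseline, so the pre-trial value is the natural reading.

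**Other-hospital admission is also asked at baseline**, so that value may be the one meant. This is fair. The concern is limited to values recorded at 4 or 9 months. For length of stay, the timing problem is plain but its consequence is unproven.

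**Conclusion.** The point holds for the older-adult outcomes. As written, the ASCOT model conditions on a consequence of allocation that is nearly a copy of arm, and its arm coefficient would not be the intention-to-treat effect that the plan promises.

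Under the three illustrative dose spreads the variance rises 3.25 to 37 times. Power falls from about 50% to about 5–12% in the simulated percentage scenarios and to 7–9% with counts. The most favourable case worked, doses from 20% to 100% with none of the effect running through dose, still leaves only 19%. Bias ranges from none (no effect through training), through an estimate of about 0.3 to 0.4 SD for a true 0.5 SD (counts, full mediation), to nearly complete loss (percentage, full mediation).

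These sizes rest on assumed dose distributions, on zero dose in controls, and on an analysis of site means that leaves out the other covariates. Length of stay and later other-hospital admission are cautions without a size. No error is shown in the KAMA model.

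**What to change.** 1. In the primary older-adult models, drop the training counts and both length-of-stay variables. Limit other-hospital admission to the value at recruitment. Keep only covariates that allocation cannot alter, for example state, age, sex and reason for stay.
2. State that older people's baseline ASCOT is measured after randomisation and after training, since the plan adjusts continuous outcomes for baseline values. Report the model with and without it.
3. Use dose only in a separate analysis labelled exploratory, noting that its information comes from five intervention sites.
4. As a clarification for the KAMA model, state that abuse-case and referral covariates use only the 9 pre-trial months.

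The cost is a revised Table 2 and matching wording in the analysis plan. All the data are already scheduled for collection. If dose was never meant for the primary model, one sentence saying so settles the main part of the point.
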